# Evaluation of a novel device for the management of high blood pressure and shock in pregnancy in low-resource settings: study protocol for a stepped-wedge cluster-randomised controlled trial (CRADLE-3 trial)

**DOI:** 10.1186/s13063-018-2581-z

**Published:** 2018-03-27

**Keywords:** Stepped-wedge cluster-randomised controlled trial, Complex intervention, Vital signs, Blood pressure, Pre-eclampsia, Obstetric sepsis, Obstetric haemorrhage, Eclampsia, Maternal death, Hysterectomy

## Abstract

**Background:**

Obstetric haemorrhage, sepsis and pregnancy hypertension account for more than 50% of maternal deaths worldwide. Early detection and effective management of these conditions relies on vital signs. The Microlife® CRADLE Vital Sign Alert (VSA) is an easy-to-use, accurate device that measures blood pressure and pulse. It incorporates a traffic-light early warning system that alerts all levels of healthcare provider to the need for escalation of care in women with obstetric haemorrhage, sepsis or pregnancy hypertension, thereby aiding early recognition of haemodynamic instability and preventing maternal mortality and morbidity. The aim of the trial was to determine whether implementation of the CRADLE intervention (the Microlife® CRADLE VSA device and CRADLE training package) into routine maternity care in place of existing equipment will reduce a composite outcome of maternal mortality and morbidity in low- and middle-income country populations.

**Methods:**

The CRADLE-3 trial was a stepped-wedge cluster-randomised controlled trial of the CRADLE intervention compared to routine maternity care. Each cluster crossed from routine maternity care to the intervention at 2-monthly intervals over the course of 20 months (April 2016 to November 2017). All women identified as pregnant or within 6 weeks postpartum, presenting for maternity care in cluster catchment areas were eligible to participate. Primary outcome data (composite of maternal death, eclampsia and emergency hysterectomy per 10,000 deliveries) were collected at 10 clusters (Gokak, Belgaum, India; Harare, Zimbabwe; Ndola, Zambia; Lusaka, Zambia; Free Town, Sierra Leone; Mbale, Uganda; Kampala, Uganda; Cap Haitien, Haiti; South West, Malawi; Addis Ababa, Ethiopia). This trial was informed by the Medical Research Council guidance for complex interventions. A process evaluation was undertaken to evaluate implementation in each site and a cost-effectiveness evaluation will be undertaken.

**Discussion:**

All aspects of this protocol have been evaluated in a feasibility study, with subsequent optimisation of the intervention. This trial will demonstrate the potential impact of the CRADLE intervention on reducing maternal mortality and morbidity in low-resource settings. It is anticipated that the relatively low cost of the intervention and ease of integration into existing health systems will be of significant interest to local, national and international health policy-makers.

**Trial registration:**

ISCRTN41244132. Registered on 2 February 2016.

Prospective protocol modifications have been recorded and were communicated to the Ethics Committees and Trials Committees. The adapted Standard Protocol Items: Recommendations for Interventional Trials (SPIRIT) Checklist and the SPIRIT Checklist are attached as Additional file 1.

**Electronic supplementary material:**

The online version of this article (10.1186/s13063-018-2581-z) contains supplementary material, which is available to authorized users.

## Background

Approximately 800 women die in pregnancy or childbirth every day [1]. Obstetric haemorrhage (antepartum and postpartum), sepsis and hypertension in pregnancy account for more than 50% of maternal deaths worldwide, 99% of which occur in low- and middle-income countries (LMICs) [1]. Early detection and effective management of these conditions relies on vital sign monitoring, including pulse and blood pressure [2]. Strategies aiming to improve the detection of haemodynamic instability are vital in recognising women in need of urgent medical care.

There are simple, cost-effective and established interventions to save lives for each of these pregnancy-related conditions, but the barrier to initiating treatment lies in recognition of maternal haemodynamic compromise and access to interventions [3, 4]. Accurate blood pressure measurement is essential for detecting and monitoring pre-eclampsia, enabling antihypertensive and prophylactic anticonvulsant therapy, appropriate transfer to higher-care facilities for timed delivery and, thereby, prevention of maternal and perinatal mortality and morbidity; however, the majority of blood pressure devices that are commercially available either fail validation in pregnancy or their accuracy is unknown [5]. In LMICs, hypertension is frequently under-detected, not only because of poor availability of working and accurate blood pressure devices, but also because of inadequate training [6, 7]. Vital sign measurement is equally critical in the management of obstetric haemorrhage and sepsis [2]. Postpartum haemorrhage, the leading cause of maternal mortality in LMICs [1], can cause death within a few hours, but effective interventions are available and early recognition facilitating immediate intervention is often lifesaving [8].

The CRADLE Research Group proposes that the introduction of the CRADLE Vital Sign Alert (VSA) device, a vital-sign-measuring device and alert tool, integrated with the CRADLE training package, will aid the early recognition of haemodynamic instability secondary to haemorrhage, sepsis and pre-eclampsia in LMICs. The CRADLE VSA device has been validated as accurate for use in pregnancy, including in women with pre-eclampsia [9] and is the first device to be validated as accurate in pregnant women with low blood pressure; from example, from haemorrhage or sepsis [10]. It has been designed to be robust and longer lasting for use in community and health facility environments in LMIC settings [9, 10]. The device is affordable, easy-to-use (including for community healthcare providers), reliable and portable. The CRADLE Group has incorporated a traffic-light early warning system into the device alerting users to hypertension and shock.

This protocol describes the stepped-wedge cluster-randomised controlled trial to assess the implementation and clinical usefulness of the CRADLE intervention in LMICs.

## Methods

### Feasibility phase: November 2015 – March 2016

The trial was preceded by a mixed-methods feasibility phase. The aim was to explore the acceptability and feasibility of the CRADLE intervention and its implementation strategies in three non-trial sites representative of the 10 main trial clusters (Ramdurg, Belgaum, India, Bishoftu, Ethiopia, Masvingo, Zimbabwe). Simultaneously, the 10 main trial clusters collected primary outcome data to evaluate the methods of data collection, and to inform the randomisation programme and the sample size calculation. Results were used to optimise the final CRADLE-3 protocol including training materials and implementation strategy for the main trial.

### Definitive stepped-wedge cluster-randomised controlled trial: April 2016 – November 2017

#### Aim

The primary aim of the trial was to determine whether implementation of the CRADLE intervention to community and facility maternity care reduces a composite of (all-cause) maternal mortality or major morbidity by ≥ 25%.

The trial is complemented by simultaneous process evaluation informed by the Medical Research Council (MRC) guidance. The aim of the process evaluation is: (1) to explore if the CRADLE trial was delivered as intended (fidelity, dose and adaptation); (2) to understand whether, how and why the intervention had an impact, through exploring healthcare provider (HCP) perspectives of their usual care and of the intervention and (3) to explore if the results are likely to be scalable and sustainable. This will include an evaluation of cost-effectiveness.

#### Design and study setting

The CRADLE-3 trial was a pragmatic, mixed-methods, multicentre, stepped-wedge cluster-randomised controlled trial of the introduction of the CRADLE intervention (CRADLE VSA device and CRADLE training package) to routine maternity care settings in LMICs. It was informed by the MRC guidance for evaluation of complex interventions [11].

Ten clusters were identified to take part in the trial. Each cluster comprised a secondary or tertiary health facility with multiple satellite primary care centres that referred to the central hospital:Gokak, Belgaum, IndiaHarare, ZimbabweNdola, ZambiaLusaka, ZambiaFree Town, Sierra LeoneMbale, UgandaKampala, UgandaCap Haitien, HaitiSouth West, MalawiAddis Ababa, Ethiopia

Each randomisation cluster crossed over from control to the CRADLE intervention at 2-monthly intervals (Figs. 1 and 2 and Additional file 1). At the time each cluster was randomised to receive the CRADLE intervention, all levels of healthcare providers within that cluster, involved in the care of pregnant/postpartum women, had access to the CRADLE intervention. The intervention effect will be determined by comparing data points in the intervention section of the wedge with those in the controlled section.

**Fig. 1 Fig1:**
[figure not shown]
Stepped-wedge cluster-randomised controlled trial design. A schematic representation of the trial design

**Fig. 2 Fig2:**
[figure not shown]
Standard Protocol Items: Recommendations for Interventional Trials (SPIRIT) Figure

#### Participants

##### Inclusion criteria

Women identified as pregnant or within the 6-week postpartum period, presenting for antenatal, intrapartum or postpartum care in cluster catchment areas* within the trial time frame.

*Catchment areas were defined in collaboration with local principal investigators, and included the major outreach facilities that result in women being assessed and referred to a defined central facility/ies. These were defined prior to randomisation and remained constant throughout the study period.

There were no exclusion criteria.

#### Intervention

The CRADLE intervention consisted of two components and is described according to the TIDieR Checklist [12].

#### Microlife® CRADLE Vital Sign Alert (VSA) device

The Microlife® CRADLE VSA is a hand-held, upper-arm, semi-automated device that measures blood pressure and pulse. The device has undergone extensive testing for accuracy and is one of few blood pressure devices to have been validated as accurate in pregnancy, including in pre-eclampsia and hypotension [10], as well as non-pregnant adults [13].

The device incorporates a traffic-light early warning system that alerts all levels of HCP to abnormalities in blood pressure and pulse secondary to obstetric haemorrhage, sepsis and pregnancy hypertension. The thresholds that trigger the traffic lights were determined through prediction studies [14, 15]. The traffic light early warning system triggers are shown in Fig. 3. A ‘red light’ and ‘up arrow’ displayed following vital signs measurement of a pregnant/postpartum woman indicate severe hypertension and should prompt intervention and/or referral. Likewise, a ‘red light’ and ‘down arrow’ with haemorrhage or sepsis should prompt immediate action. A ‘yellow light’ and either ‘down arrow’ or ‘up arrow’ indicate less urgent need for assessment, intervention and/or referral. It is proposed that the traffic lights will alert users to abnormal vital signs, including those without formal healthcare training. This should enable earlier management to improve outcomes that would directly benefit the woman and her unborn/newborn child.

**Fig. 3 Fig3:**
[figure not shown]
Vital Signs Alert (VSA) device traffic-light early warning system display options. Legend: *SBP* systolic blood pressure; *DBP* diastolic blood pressure; SI Shock Index

The production costs are less than US$20 per unit and has been designed to be simple to use, even by unskilled personnel after minimal training. The device fulfils the World Health Organisation requirements for automated devices used in low-resource settings [13]. Other developments suited to LMICs include a micro-USB charging ability. The CRADLE VSA is manufactured in Taiwan.

As part of the CRADLE-3 trial intervention, the CRADLE VSA was incorporated into routine maternity care. Primary, secondary and tertiary facilities were allocated devices according to their delivery rate, staffing numbers and number of beds per ward. Pre-existing blood pressure measurement devices were removed from clinical areas unless existing equipment had functionality designed for that area, e.g. repeated automated measures in an operating theatre or a high dependency area, and this was left to the discretion of the lead clinician.

#### CRADLE training package

The intervention users included every cadre of healthcare professional involved in maternity care within the cluster. This included community healthcare providers (cHCPs) where they were supported at district level and involved in provision of routine maternity care. The CRADLE research group created a simple CRADLE training package for prospective CRADLE VSA users.

The training package consisted of short animated films, an interactive session, action prompt cards attached to the CRADLE VSA and posters. There were two sets of training materials available, one for facility HCP (fHCPs) and one for cHCP with very limited resources or no formal training. All materials were translated into local language where required.

The CRADLE package content covered:How to use the CRADLE VSAMaintenance of the CRADLE VSABasic overview of clinical assessment and management of pre-eclampsia/eclampsia and shock in relation to the traffic-light alerts

At the randomised time point the local implementation team (clinical research officers responsible for ongoing CRADLE outcome data collection and site principal investigators) attended face-to-face one-off training with the research team lasting approximately 5 h. The implementation team and research team subsequently delivered one-off group training sessions lasting 2–4 h to local stakeholders and representative HCP from each of the clinical areas in the cluster.

Attendees were given training materials and CRADLE VSA to disseminate to their clinical areas. The implementation team continued to visit clinical areas regularly to collect outcome data therefore providing ongoing support to HCP.

The core components of the intervention (the CRADLE VSA, animated films, posters and content of the training presentation) were standardised across all clusters. Delivery of the core components could be adapted to meet the needs of the cluster.

#### Control

This intervention was compared to routine maternity care. This involved blood pressure monitoring with a variety of blood pressure devices that were available locally and management according to local guidelines.

#### Primary outcome

The rate of a composite of maternal mortality or major morbidity (one of maternal death, eclampsia or emergency hysterectomy with no double counting per 10,000 deliveries in each cluster each month). We will report the effect of the intervention on the primary endpoint, on each of the three components, and on each of the secondary endpoints.

*Maternal death* was defined as death during pregnancy or within 42 days of delivery (or last contact day if contact not maintained to 42 days).

*Eclampsia* was defined as occurrence of generalised convulsions with increased blood pressure during pregnancy, labour or within 42 days of delivery in the absence of epilepsy or another condition predisposing to convulsions.

*Emergency hysterectomy* was defined as surgical removal of all or part of the uterus.

#### Secondary outcomes

Maternal deaths from all causes were collected with additional information regarding the cause of maternal death collected to determine the potential for impact of the CRADLE VSA. The percentage of deaths that occurred as a result of obstetric haemorrhage, pregnancy-related sepsis and hypertensive disorders of pregnancy will be presented across all clusters pre and postintervention with adjusted risk ratios (RRs). If there are other large groups of other clinically important causes of death, e.g. early pregnancy complications, these will also be defined.

Maternal secondary outcome measures:Intensive care unit admission, defined as any admission to a specific intensive care unit or an equivalent highest-level care environment within the trial area (or referral to the highest level care facility outside of the area) in areas where an intensive care unit does not existStroke, defined as hemiparesis and/or blindness developed during pregnancy or in the 42 days postpartum lasting longer than 48 hCause of intensive care admissionCause of maternal deathCause of emergency hysterectomyPlace of eclamptic fitPlace of maternal death

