### Sample size calculation

Sample size estimation has been carried out by the CRADLE statistician, using Stata version 13.1 and the methods of Hemming and Girling [16]. This was informed by data from the feasibility phase. For the purpose of the power calculation an assumption that there are at least 4000 deliveries per centre per month was made (or 8000 per cluster period of 2 months) and at least nine clusters, each observed for 20 months (10 time periods of 2 months each). We anticipated a baseline event rate of 1% and anticipate a 25% reduction in this to 0.75% post intervention. We would require a total of 6300 outcome events, with a coefficient of variation of 0.4 and an Intra Cluster Correlation of 0.0085, to have power of 99%. We would require a total of 2450 outcome events with a coefficient of variation of 0.4, to have power of 95%.

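### Risk ratios for cause of death are attached to shares of maternal deaths, a denominator the intervention is meant to change, so they do not measure its effect on cause-specific death

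*Protocol article*

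**What the plan says.** In the protocol article, Secondary outcomes, the plan for cause of maternal death reads: "The percentage of deaths that occurred as a result of obstetric haemorrhage, pregnancy-related sepsis and hypertensive disorders of pregnancy will be presented across all clusters". The sentence continues: "pre and postintervention with adjusted risk ratios (RRs"). Cause information was gathered "to determine the potential for impact of the CRADLE VSA". Further cause groups may be added: "If there are other large groups of other clinically important causes of death, e.g. early pregnancy complications, these will also be defined".

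Elsewhere the denominator is deliveries. The primary outcome counts "one of maternal death, eclampsia or emergency hysterectomy with no double counting per 10,000 deliveries in each cluster each month", and stillbirths and neonatal deaths are likewise expressed per 10,000 deliveries. The Primary outcome and Statistical plan sections also promise an effect estimate for each component of the composite, so all-cause maternal death is analysed separately. The article nowhere states a cause-specific death rate per delivery.

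**The concern.** On the plain reading, the adjusted risk ratio belongs to the percentage of deaths. That percentage has an outcome in both numerator and denominator. A change in one cause alters the total, and through the total it moves the share of every other cause. The resulting ratio answers how the mix of causes among women who died has shifted. It does not answer whether a woman's risk of dying from haemorrhage, sepsis or a hypertensive disorder has changed.

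What is at stake is the reading of the one mortality analysis that separates the causes the device targets from the rest. A real reduction could look smaller than it is or disappear, and an untouched cause could appear to worsen. Any extra cause groups that are added would be open to the same artefact.

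**Working it through.** **The plan's own figures.** The article gives no figure for the cause-of-death comparison. Two of its inputs are used here.
- Effect size: "We anticipated a baseline event rate of 1% and anticipate a 25% reduction in this to 0.75% post intervention", a ratio of 0.75/1.00 = 0.75 for the composite. It fits the plan's event total: 9 clusters × 10 periods × 8000 deliveries × (0.01 + 0.0075)/2 = 6300. Applying 25% to deaths from particular causes is an assumption.
- Cause mix: the three conditions "account for more than 50% of maternal deaths worldwide" (Background). I take 50% as the base. The values 60%, 70% and 75% are assumed, to show the range.

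**Identity.** For crude rates, a cause's share of deaths is its death rate per delivery divided by the all-cause death rate per delivery. Hence

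share RR = (cause-specific RR per delivery) / (all-cause RR per delivery).

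The two ratios agree only when the all-cause RR is 1. An all-cause RR below 1 pushes the share RR upwards, and one above 1 pushes it downwards.

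**Targeted causes fall, others unchanged.** Let s be the share of deaths from causes that fall by a fraction r.
- All-cause RR = 1 − s·r
- Share RR of a falling cause = (1 − r)/(1 − s·r)
- Share RR of an unchanged cause = 1/(1 − s·r)

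With r = 0.25:

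| s | All-cause RR | True RR, targeted | Share RR, targeted | Share RR, unchanged cause (true RR 1.00) |
|---|---|---|---|---|
| 0.50 | 0.875 | 0.75 | 0.857 | 1.143 |
| 0.60 | 0.850 | 0.75 | 0.882 | 1.176 |
| 0.70 | 0.825 | 0.75 | 0.909 | 1.212 |
| 0.75 | 0.8125 | 0.75 | 0.923 | 1.231 |

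In the first row the targeted share goes from 50.0% to 0.375/0.875 = 42.9%, so a 25% fall reads as about 14%.

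**All causes fall equally.** Share RR = 0.75/0.75 = 1.00 for every cause.

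**Only haemorrhage deaths fall by 25%.** Assume shares of 25% haemorrhage, 10% sepsis, 20% hypertensive disorders and 45% other. The total becomes 0.25 × 0.75 + 0.75 = 0.9375. Haemorrhage shows 0.75/0.9375 = 0.80. Sepsis and hypertensive disorders, both unchanged, show 1/0.9375 = 1.067.

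**Reversal.** With s = 0.50 and targeted deaths down 25%, let other deaths rise by 30%. The total is 0.375 + 0.65 = 1.025 and the share RR is 0.75/1.025 = 0.732, which slightly overstates the fall. With a 10% rise the total is 0.925 and the share RR is 0.811, which still understates it.

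**The case against.** **The sentence may intend something else.** It does not name the denominator of the risk ratio. Cause of maternal death is a listed secondary outcome, and the Statistical plan promises effects on secondary outcomes from a model that weights each woman equally. A table of percentages beside woman-level risk ratios is therefore a possible reading, and it is close to the fix. But it is not written. The risk ratios are attached to the percentage, and no per-delivery cause-specific rate appears. If that reading is intended, one clause settles the matter.

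**The percentage is a sensible summary.** This stands. How much mortality lies in causes the device could address is properly a share of deaths, and that fits the stated aim of judging potential for impact. The fault lies in attaching an adjusted risk ratio to the share.

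**All-cause death is analysed separately.** This also stands and limits the harm: an equal fall in all causes would show there. A reader could even multiply the share ratio by the all-cause ratio. That works for crude ratios, but adjusted estimates from separate models need not multiply, and no confidence interval follows.

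**Odds ratios come first in the Statistical plan.** The Secondary outcomes sentence specifies risk ratios, and odds ratios of shares would not repair the measure. At s = 0.50 the odds ratio of the combined targeted share does return (0.429/0.571)/1 = 0.75. But it is 1.00 if all causes fall equally. In the haemorrhage-only example, unchanged sepsis still shows (0.1067/0.8933)/(0.10/0.90) = 1.07.

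**Stronger readings.** A reader might infer that a fall in one cause forces every other share up. It does not: the remaining shares rise only in sum, and all three targeted shares fall together in the table above. Nor does the bias always hide benefit, as the reversal shows. The documents also do not support the inference that the mortality results as a whole are compromised, because all-cause death has its own analysis.

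**Conclusion.** Wrong as written, for a secondary outcome. The measure does not estimate the effect on cause-specific death, whatever the cause mix. The direction and size of the distortion are conditional. When total deaths fall, the share ratio understates reductions in targeted causes and shows a rise in unchanged ones; when other deaths rise enough, it errs the other way.

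The numerical results are illustrations. They rest on carrying the composite's 25% over to cause-specific deaths and on a cause mix that the article gives only as a worldwide lower bound. The 25/10/20/45 split is wholly assumed, and nothing in the article shows whether an apparent rise of 7% would be distinguishable from chance. The primary outcome, its components and the power calculation are unaffected.

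**What to change.** State that the effect on deaths from obstetric haemorrhage, from pregnancy-related sepsis and from hypertensive disorders will each be estimated per 10,000 deliveries with the primary outcome's model: odds ratio first, risk ratio if the log link converges, as the Statistical plan already sets out. Treat any added cause group the same way. Keep the percentage of deaths by cause, before and after the intervention, as a descriptive table without risk ratios.

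No new data are needed, and the article still describes this analysis in the future tense. The cost is statistical. Cause-specific deaths are a subset of one component of the composite, so estimates will be imprecise. With ten centres, the primary model carries 10 centre effects + 10 linear trends + 1 intervention effect = 21 parameters, and the Statistical plan itself warns of poor convergence with the log link. A simpler model for use on non-convergence should be named in advance. Keeping the share would not avoid this sparsity, because the same cause-specific counts form its numerator.
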